#### Data analysis

Quantitative data from study databases will be summarized using simple descriptive statistics including frequencies, measures of central tendency, and variability along with data visualization methods, such as frequency tables, bar charts, line graphs, and scatter plots to understand patterns and characteristics of testing uptake, exposures, and symptoms and to guide adaptive implementation. Missingness in data will be examined via sensitivity analysis and imputation methods will be applied when appropriate. Parametric and non-parametric tests will be employed to compare the survey responses between the clinics while controlling for a variety of demographic and socioeconomic variables, including the FQHC clinic cluster. Data collected at the point of test distribution (collected by study coordinators, promotores, and vending machines) will be used to evaluate implementation strategy effectiveness on testing uptake. Hierarchical multilevel models will be used to ensure the inclusion of random effects, variation between clusters, variation between times within clusters, and the fixed effect of time which will be estimated independently of treatment effect so that systematic change over time will not be mistaken for effect of treatment. This is key, based on significant variations in testing uptake observed during previous COVID-19 variant waves. To account for potential within-clinic correlation, data will be reduced for each cluster to a single observation, and then subject to standard two-sample analyses. Secondary analyses will be conducted to determine the appropriateness of the test type distribution within the context of symptom onset and exposure time frame.

Rapid matrix analysis of patient/community member and provider/staff interviews and periodic reflections will be conducted to identify key concerns and opportunities for refinements. This information, along with data about the implementation of the strategy bundle and testing results, will be summarized and presented to the CSAB (two sessions after Clinic 1 roll-out and one session after each consecutive clinic roll-out). A list of possible refinements will be identified based on input from the CSAB and final decisions about refinements will be made by the community-clinical-research team. Any changes made to the strategy bundle and procedures will be documented in the Adaptation documentation database. After refinements to the multi-component strategy bundle have been completed, the PRISM Fit Assessment will be conducted with the next clinic to allow for clinic-specific further adjustments. A matrix approach will be used to triangulate data from quantitative and qualitative sources using the key domains of PRISM. A joint display will also be produced to support the integration of data sources [21, 22].

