### Aims

The specific aims of the study are as follows:

#### Aim 1

To refine and operationalize a multi-component implementation strategy bundle and a related set of outcome metrics for COVID-19 testing.

#### Aim 2

To implement and evaluate the impact of the innovative, multilevel, and multicomponent implementation strategy bundle to optimize COVID-19 rapid testing among underserved communities in Central and South San Diego using a roll-out implementation optimization study design across 4 clinics over 18 months.

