### Power size calculations

The number of participating clusters/clinics and target clinic participant enrollment for the ROIO study design was determined using cluster randomized trial sample size estimation tools. Per the ROIO study design, each clinic cluster will begin in the control group and then cross over into the intervention group at different time points and then continue with the intervention until the end of the study (see Fig. 2). Although it is anticipated that the implementation strategies as outlined by CSAB will undergo some adjustments during the implementation process, the target cluster/clinic sample size estimates are based on a stepped wedge design using serial cross-sectional evaluations of electronic medical records and test kits distributed. It is estimated that the study will have the capacity to distribute 52,000 FDA-authorized rapid antigen tests provided by the San Diego County Health and Human Services and the California Department of Public Health. The primary outcome is the increased distribution of RATs within the communities near each of the 4 clinics. This will be measured using a proxy outcome defined as the proportion of clinic patients visits to the number of RAT kits distributed per month at each participating clinic. Currently, RAT kit distribution among target clinic patients ranges from 7 to 13% (*M* = 9%) with approximately 430 kits being distributed per month between all four clinics. The aim is to increase distribution of test kits to 40% of clinic patient encounters per month, which would result in the distribution of 1822 kits per month during the final treatment sequence. Based on data collected from the phase 1 study, approximately 40% of testing uptake occurred among clinic patients and the remaining 60% from community members even when the intervention was clinic-based. It is anticipated that there will be a similar community uptake during this study. Based on the sequential rollout outlined in the Fig. 2 with rollout for Clinic 1 at month 4, Clinic 2 at month 8, Clinic 3 at month 12, and Clinic 4 at month 16, over the course of the entire study it is anticipated that a total distribution of 20,503 tests, assuming average distribution per clinic. Estimating that this will equal approximately 40% of total increase and the remaining uptake to occur among community members, a total uptake of 58,091 test kits is estimated over the course of the study. Using the Shiny CRT Calculator [24], it was determined that a minimum cluster sample size of 285 across 4 clinics will provide sufficient power (beta > 0.8) to determine an intervention proportion increase of 0.05 to 0.25 assuming the following: stepped-wedge design, cross-sectional sampling structure at each of 4 sequences (approximately every 3 months in the study), 0.5 coefficient of variation in cluster sizes (based on average number of patient encounters per month per clinic), intra-cluster correlation (ICC) of 0.02, for our binary outcome (test or no-test). It was also assumed that there will be an exchangeable cluster correlation structure as SARS-CoV-2 testing demand has been impacted significantly by changes in variant severity and transmissibility.

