
**Fig. 2 Fig2:**
[figure not shown]
Design matrix structure: one cluster per treatment sequence

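### Reducing each clinic to one observation for a two-sample test does not fit a design in which all four clinics cross over, and the plan does not rank this step against the multilevel model

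*Protocol article*

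**What the plan says.** Three parts of the protocol article bear on this.

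- **Data analysis, the model.** Effectiveness on testing uptake is to be assessed with hierarchical multilevel models. These have random effects and let uptake differ by clinic and, inside a clinic, by time. They also carry a time term, described as "the fixed effect of time which will be estimated independently of treatment effect so that systematic change over time will not be mistaken"; the aim is that a trend is not credited to the treatment. The section calls this key because uptake varied with earlier variant waves.
- **Data analysis, the next step.** The reason given for this step is "To account for potential within-clinic correlation". The step itself is that "data will be reduced for each cluster to a single observation, and then subject to standard two-sample analyses". The two samples are not named, time is not mentioned, and the step is not ranked against the model. Secondary analyses are introduced only in the sentence after it.
- **Power size calculations and Fig. 2, the design.** The text has it that "each clinic cluster will begin in the control group and then cross over into the intervention group at different time points". After crossing over, the clinics "then continue with the intervention until the end of the study". The caption of Fig. 2 reads "Design matrix structure: one cluster per treatment sequence". The schedule is "rollout for Clinic 1 at month 4, Clinic 2 at month 8, Clinic 3 at month 12, and Clinic 4 at month 16".

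**The concern.** Collapsing each cluster to one value and comparing two sets of values is an analysis for a parallel cluster trial, where each cluster belongs to one arm. Here no clinic is control-only or intervention-only. Taken literally, the step has nothing to compare. The nearest version that can be run is a before/after comparison of clinic means. It leaves out the time adjustment that the same paragraph calls essential. In every clinic the intervention months come after all the control months, so a rise or fall in testing demand would be counted for or against the bundle.

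The step is also unnecessary for its stated purpose, because the random effects of the multilevel model already handle within-clinic correlation. What remains is two analyses of the same effect that can disagree, with no stated priority.

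**Working it through.** The plan gives no figure for this step, so there is none to reproduce. The sample-size figures belong to the stepped-wedge calculation and do not enter here.

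**Inputs.** Starts at months 4, 8, 12 and 16 (Power size calculations). Length 18 months (Aims: "study design across 4 clinics over 18 months"), or 21 months (Aim 2 procedures). Average baseline 9%, range 7 to 13% (Power size calculations). The start month is counted as an intervention month.

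**Step 1, literal reading: one value per clinic.** With start month s and length T, the share of months under the intervention is (T - s + 1)/T.

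| Clinic | Start s | Control months (mean) | Intervention months (mean) | Gap | Intervention share, T = 18 |
|---|---|---|---|---|---|
| 1 | 4 | 1-3 (2) | 4-18 (11) | 9 | 15/18 = 83% |
| 2 | 8 | 1-7 (4) | 8-18 (13) | 9 | 11/18 = 61% |
| 3 | 12 | 1-11 (6) | 12-18 (15) | 9 | 7/18 = 39% |
| 4 | 16 | 1-15 (8) | 16-18 (17) | 9 | 3/18 = 17% |

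The result is four numbers, each a mixture of both conditions, and no two groups.

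**Step 2, one value per clinic per condition.** This gives eight values from the same four clinics, in pairs. An independent two-sample test ignores the pairing.

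The mean control month is s/2 and the mean intervention month is (s + T)/2, so the gap is T/2 in every clinic, whatever its start. For T = 18 the averages are month 5 and month 14, a gap of 9. For T = 21 the gap is 10.5. Pairing the values would therefore not remove the confounding.

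**Step 3, size of the bias.** For a linear trend of b points per month and no bundle effect, the contrast estimates (T/2) x b, that is 9b (or 10.5b).

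The documents give no trend, so the following are assumptions. Let demand in month m be 9% x f^((m-1)/17), identical in all clinics, with no bundle effect.

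- Halving (f = 0.5): control means 8.65, 7.99, 7.40, 6.87 (average 7.73%); intervention means 6.08, 5.56, 5.10, 4.69 (average 5.36%). Difference -2.4 points.
- Doubling (f = 2): control means 9.38, 10.20, 11.13, 12.16 (average 10.72%); intervention means 13.74, 14.80, 15.98, 17.29 (average 15.45%). Difference +4.7 points.

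The rule of 9b agrees: 9 x (-4.5/17) = -2.4 and 9 x (9/17) = +4.8.

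**Step 4, does a time-adjusted analysis escape this?** A simulation compared the contrast of collapsed means with a model with fixed clinic and month effects. It used 4,000 runs per scenario and assumed baseline 9%, ICC 0.02, 285 observations per clinic-month and a linear trend.

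| True effect | Trend, points per month | Collapsed contrast | Clinic-and-month model |
|---|---|---|---|
| 0 | +0.5 | +4.5 | 0.0 |
| +5 | -0.5 | +0.5 | +5.0 |

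**The case against.** **The model stays in the plan.** The Abstract names only multilevel models for determining impact, and the Discussion relies on them again for confounders. A reader might infer that the trial's effect estimate as a whole will be confounded with time. The documents do not support that: the bias affects only the collapsed analysis. This objection stands and limits the point. It does not make the sentence correct, because the sentence is neither ranked below the model nor labelled a sensitivity analysis.

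**There is a within-period reading.** One value per clinic within a period does give two groups: 1 v 3 clinics in months 4-7, 2 v 2 in months 8-11 and 3 v 1 in months 12-15. These are free of calendar-time confounding. But the text mentions no periods in this step, and such comparisons of so few non-randomised clinics are very weak. This could be a sound form for a check if it were written down; it does not rescue the sentence as it stands.

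**The sentence may refer to the survey comparisons between clinics.** It follows directly on the uptake model, and comparing four clinics with one value each would not be a two-sample problem either.

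**The illustration might be read as a false-positive result.** A t-test on the noise-free means of step 3 gives p = 0.003, but this is an artefact of identical, noise-free clinics: a fall of only 10% gives the same p. With assumed baselines of 7, 7.5, 8.5 and 13%, halving gives p from about 0.05 to 0.36, depending on clinic order and on whether the trend is multiplicative or additive. No p-value should be attached; only the bias in the estimate is claimed.

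**The analysis plan may settle it.** It may, but this is a stated method that the design cannot support, not an omitted detail.

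**Conclusion.** The sentence is wrong as written. Read literally, it cannot be carried out, because every clinic contributes to both conditions. Read as clinic means per condition, it treats paired values as independent and carries a bias of about 9 times the monthly trend (10.5 times over 21 months).

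The gap in calendar time follows from the study length alone. The figures of -2.4 and +4.7 points rest on an assumed halving or doubling of demand from 9%, the same in all clinics, with no bundle effect. The real size and direction depend on an epidemic trend that the documents do not give. The conclusion does not extend to the multilevel model, which adjusts for time.

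**What to change.** Delete the sentence. State that the multilevel model with clinic and calendar-period effects is the primary analysis of the bundle's effect, and that its random effects account for within-clinic correlation.

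If a cluster-summary check is wanted, label it a sensitivity analysis. Base it on clinic-period summaries that keep clinic and period effects, or on comparisons between clinics within the same period. It should not be a two-sample test of collapsed clinic values.

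The cost is about a sentence or two of wording, with no new data and no change to the conduct of the study.

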### Power size calculations

The number of participating clusters/clinics and target clinic participant enrollment for the ROIO study design was determined using cluster randomized trial sample size estimation tools. Per the ROIO study design, each clinic cluster will begin in the control group and then cross over into the intervention group at different time points and then continue with the intervention until the end of the study (see Fig. 2). Although it is anticipated that the implementation strategies as outlined by CSAB will undergo some adjustments during the implementation process, the target cluster/clinic sample size estimates are based on a stepped wedge design using serial cross-sectional evaluations of electronic medical records and test kits distributed. It is estimated that the study will have the capacity to distribute 52,000 FDA-authorized rapid antigen tests provided by the San Diego County Health and Human Services and the California Department of Public Health. The primary outcome is the increased distribution of RATs within the communities near each of the 4 clinics. This will be measured using a proxy outcome defined as the proportion of clinic patients visits to the number of RAT kits distributed per month at each participating clinic. Currently, RAT kit distribution among target clinic patients ranges from 7 to 13% (*M* = 9%) with approximately 430 kits being distributed per month between all four clinics. The aim is to increase distribution of test kits to 40% of clinic patient encounters per month, which would result in the distribution of 1822 kits per month during the final treatment sequence. Based on data collected from the phase 1 study, approximately 40% of testing uptake occurred among clinic patients and the remaining 60% from community members even when the intervention was clinic-based. It is anticipated that there will be a similar community uptake during this study. Based on the sequential rollout outlined in the Fig. 2 with rollout for Clinic 1 at month 4, Clinic 2 at month 8, Clinic 3 at month 12, and Clinic 4 at month 16, over the course of the entire study it is anticipated that a total distribution of 20,503 tests, assuming average distribution per clinic. Estimating that this will equal approximately 40% of total increase and the remaining uptake to occur among community members, a total uptake of 58,091 test kits is estimated over the course of the study. Using the Shiny CRT Calculator [24], it was determined that a minimum cluster sample size of 285 across 4 clinics will provide sufficient power (beta > 0.8) to determine an intervention proportion increase of 0.05 to 0.25 assuming the following: stepped-wedge design, cross-sectional sampling structure at each of 4 sequences (approximately every 3 months in the study), 0.5 coefficient of variation in cluster sizes (based on average number of patient encounters per month per clinic), intra-cluster correlation (ICC) of 0.02, for our binary outcome (test or no-test). It was also assumed that there will be an exchangeable cluster correlation structure as SARS-CoV-2 testing demand has been impacted significantly by changes in variant severity and transmissibility.

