#### Vending machines that dispense no-cost self-testing kits

Vending machines located outside of clinics will provide interactive instructions in Spanish and English for accessing no-cost self-administered COVID-19 test kits. The vending machines will be available 7 days/week and will be accessible to the public. The vending machine locations will be identified with guidance from the partner FQHC to consider potential workflow and service implications. Study registration and consent will be required to obtain a test kit from the vending machines. Alternative sources for testing kits will be provided for individuals who do not want to register and consent to the study.

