### Participants

Recruitment of community members will occur at the FQHC clinics through collaborative efforts between promotores, and on-site research staff. Recruitment and outreach will occur on-site for patients coming to the clinic for appointments, through outreach at local community gathering locations, phone calls, and/or emails to existing FQHC patients, outreach by CSAB members utilizing their existing networks, social media posts, flyers, and/or billboards. It is anticipated that participants will represent the ethnic, racial, and sex distributions of the registered patients at each participating clinic. Promotores will be hired by the partnering FQHC and speak the languages that are most common in the local communities and clinics (Spanish and English).

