#### Data collection

Quantitative and qualitative data will be collected using multiple databases and methods. Data collection methods are summarized in Table 2 with the data source name, type of data collected, origin of data and timing for data collection, and associated PRISM domains assessed. Data from the PRISM Fit Assessment will be summarized as descriptive statistics and displayed in the form of bar graphs to inform the group action planning discussion. Key implementation and clinical and public health effectiveness outcomes are summarized in Table 3. The timing for each data collection method is also noted in Fig. 1. Participants will be required to provide contact information and minimum symptom and exposure data prior to obtaining rapid tests and the type of test and timing of testing will be captured for both the walk-up onsite testing and vending machine testing along with basic demographics. Participants will also be invited to provide rapid test results and receive personalized health counseling based on their test result.

**Table 2 Tab2:** Data sources, data types, origin and PRISM domains

Data source name	Type	Origin/timing	PRISM domains
REDCap study database for rapid COVID-19 testing (QUAL + QUANT)	Database completed by walk-up onsite testing staff about number of tests completed, reason and timing for testing including symptoms and exposure, community member demographics	Walk-up onsite testing staff Ongoing	Reach Implementation Maintenance
Preventive care status and health characteristics (QUANT)	Electronic health records data on primary and secondary outcomes, participant demographics, other health characteristics	SYH Research Assistant accessing electronic health records After each initial roll-out	Reach Recipient characteristics Effectiveness
Promotore support activities database (QUAL + QUANT)	# of days and hours promotore services are provided; # and type of support activities	Promotores Ongoing	Adoption Implementation Maintenance
Vending machine automatic data log (QUANT)	#, timing, type of interactions with vending machine; reason and timing for testing, type of test used; participant demographics	Programmed in vending machine Ongoing	Reach Effectiveness Implementation Maintenance

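### The primary outcome is about communities near each clinic, but kits are counted at the clinic that dispenses them, so kits taken by residents of not-yet-started areas are credited to the wrong community

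*Protocol article*

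**What the plan says.** Under Power size calculations, the protocol article names the outcome by community: "The primary outcome is the increased distribution of RATs within the communities near each of the 4 clinics". The next sentence gives the measure, a proxy: "proportion of clinic patients visits to the number of RAT kits distributed per month at each participating clinic". Data analysis confirms where the data arise: "Data collected at the point of test distribution (collected by study coordinators, promotores, and vending machines) will be used to evaluate implementation strategy effectiveness".

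On access, the vending machine section says "The vending machines will be available 7 days/week and will be accessible to the public", and the condition it sets is "Study registration and consent will be required to obtain a test kit from the vending machines". Participants lists recruitment on site at the clinics, calls and emails to existing patients of the health center, and "outreach by CSAB members utilizing their existing networks, social media posts, flyers, and/or billboards". Power size calculations expects about 40% of uptake from clinic patients and 60% from other community members. Roll-out is at months 4, 8, 12 and 16, and each clinic is a control until its own start.

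Data collection adds: "Participants will be required to provide contact information and minimum symptom and exposure data prior to obtaining rapid tests". The article describes no use of that information to place a kit in a community. Its limitations paragraph covers the non-randomized order but not use of one clinic's kits by another clinic's community.

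**The concern.** The outcome and its measure use different units. The outcome belongs to the area where people live; the count belongs to the place where the kit is dispensed. They agree only if people take kits at their own clinic. Nothing stated ensures this: all four clinics belong to one organization in Central and South San Diego, the machines are public, and most expected uptake is from non-patients.

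The design depends on the comparison across clinics. Data analysis wants time estimated separately from treatment because variant waves moved testing uptake. Clinics not yet live, observed in the same months as live ones, supply that separation, and those are the months in which cross-use is possible. Adjusting for clinic or participant covariates does not move a kit back to the cluster it came from. At stake is whether the estimate can be read as what the bundle did in each clinic's own community.

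**Working it through.** **Inputs from the documents.** Table 1 kits per month: 196 + 125 + 61 + 48 = 430, matching the stated 430. Target: 1,822 kits at 40% of encounters, so 1,822 / 0.40 = 4,555 encounters per month. Baseline: 430 / 4,555 = 9.4%, consistent with the stated mean of 9%. Table 1 patients: 18,124, 20,102, 8,328 and 8,120 (total 54,674).

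**Assumptions.** The documents give no diversion rate *s*, no distances between clinics and no encounters per clinic. I take *s* from 0 to 50% and share the 4,555 encounters in proportion to Table 1 patients. This gives about 1,510, 1,675, 694 and 676 encounters, and baselines of 196/1,510 = 13.0%, 125/1,675 = 7.5%, 61/694 = 8.8% and 48/676 = 7.1%. That matches the stated range of 7 to 13%.

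**When cross-use is possible.** Control clinic-months: 3 + 7 + 11 + 15 = 36. Those from month 4 on, when at least one clinic is live: 0 + 4 + 8 + 12 = 24. This counts opportunity only; it does not measure cross-use.

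**Case A: cross-use displaces control-clinic kits.** Over 4 clinics and 18 months, control clinics dispense their baseline and live clinics 40 kits per 100 encounters. From month 4, a share *s* of each control clinic's kits moves to the live clinics, split equally among them. Kits per 100 encounters are then fitted with clinic effects, month effects and one treatment effect. The estimate is linear in *s*:
- Table 1 sizes: 31.18 + 14.46*s*
- Four equal clinics with baseline 9: 31.0 + 21.6*s*

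| Diversion *s* | Table 1 sizes | Change | Equal clinics | Change |
|---|---|---|---|---|
| 0 | 31.2 | 0 | 31.0 | 0 |
| 5% | 31.9 | +2% | 32.1 | +3% |
| 10% | 32.6 | +5% | 33.2 | +7% |
| 20% | 34.1 | +9% | 35.3 | +14% |
| 50% | 38.4 | +23% | 41.8 | +35% |

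The Table 1 columns are smaller because Clinic 1, live first, is large and the two clinics that start last are small: what they lose is a small amount per encounter at the live clinics.

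**Case B: cross-use displaces nothing.** Take four equal clinics with 4,555 / 4 = 1,139 encounters and 430 / 4 = 107.5 baseline kits. A live clinic gives 0.40 × 1,139 = 455.5 patient kits. If these are 40% of its total, the total is 1,139 and 683 are community kits. The contrast by dispensing site is (1,139 − 107.5) / 1,139 = 0.906 kits per encounter, whatever *s* is. Here *s* is the share of live-clinic community kits taken by residents of not-yet-started areas. With *k* clinics live, the contrast by residence is

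[(1,139 − 683*s*) − (107.5 + 683*s* × *k*/(4 − *k*))] / 1,139.

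| *s* | 1 live | 2 live | 3 live |
|---|---|---|---|
| 10% | 0.826 | 0.786 | 0.666 |
| 20% | 0.746 | 0.666 | 0.426 |

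The site count exceeds the residence contrast by factors of 1.10, 1.15 and 1.36 at 10%, and 1.21, 1.36 and 2.13 at 20%. The kits are real. What differs is the community they belong to.

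**The case against.** The article openly calls its measure a proxy, and it gives no evidence that anyone will cross between clinics. These replies stand in part:

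- **Contamination.** A reader might infer that the control periods are contaminated. The documents support only a risk of unknown size.
- **Outreach.** A reader might call it unrestricted. The article lists channels and is silent on timing. It bases recruitment at the clinics and ties full-time promotores to each clinic's own first 3 months. A condensed article may leave the outreach schedule to the full protocol.
- **Displacement.** The 9% baseline is described for clinic patients. A non-patient near Clinic 4 who uses Clinic 1's machine may never have been in Clinic 4's count, so inflation by displacement is not shown. Extra demand at control clinics would pull the estimate the other way.
- **Numerator.** It is unclear whether community kits enter the proxy, because the 40% target is set against patient encounters and community uptake is added on top. If only patient kits count, most cross-use drops out, but the proxy then does not measure the stated community outcome.

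None of this removes the mismatch between the outcome and its measure, which lies in two adjoining sentences and does not depend on anything the article left out.

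**Conclusion.** The point holds as a mismatch of units with an unmeasured consequence. Kits can be credited to the wrong community, and nothing in the article detects or corrects it.

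With displacement, the overstatement is about 2% to 9% for diversion of 5% to 20%, and 23% at 50%, given Table 1 clinic sizes and encounters proportional to patients. The larger figures of 14% and 35% need four equal clinics, which Table 1 contradicts. Every diversion rate is an assumption. Without displacement, the count is right in total and wrong by place.

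A reader might go further and infer that the planned rise from 9% to 40% could be produced by cross-use. The figures do not support that: even 50% diversion adds about 7 kits per 100 encounters (38.4 − 31.2) to a contrast of 31. Nor do the documents justify requiring outreach to be held back until each clinic starts. They do not say how outreach is timed, and delaying it is a trade-off with reach.

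**What to change.** 1. Derive a home area for each registered kit: ZIP code, or the home clinic for patients of the health center. This uses the contact information already required and assumes that it includes, or can include, one of these.
2. Report each month the share of kits at live clinics that went to residents of areas not yet live.
3. Keep the dispensing-site analysis, and add a sensitivity analysis that reassigns those cross-area kits to the home area or excludes them.
4. Describe the dispensing-site result as a clinic-site effect unless cross-area use is shown to be small.

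The cost is one derived field, one monthly tabulation and one extra analysis. There are two limits. Registration is described for walk-up and vending kits, so home area may be missing for kits handed out before roll-out. Clinic visits are also not a natural denominator for counts by residence. For both reasons the home-area result should be a sensitivity analysis and not a replacement for the site analysis. No change to outreach is asked for.
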